#### Control intervention

Participants allocated to the control intervention will be signposted to the website of ‘Beat’ [21], a reputable UK ED charity which provides information, resources and support for eating disorders. Participants in this group will be able to access the FREED-M intervention after the end of the trial.

### Interviews

An estimated sample of around 20 participants, depending on inductive thematic saturation [93], will take part in qualitative interviews about their experience of the intervention. Interviews will be based on a specifically designed semi-structured topic guide (see Appendix 1) trying to comprehensively capture people’s views and will explore attitudes towards the recruitment methods and study design, initial expectations of the intervention, perceived strengths and weaknesses, engagement and suggestions for enhancing acceptability and relevance. Participants will be recruited purposively from the intervention group, e.g. according to gender, age and baseline ED symptoms, to capture a broad range of participants with potentially different experiences. Participants will be approached for these interviews at the 12-week post-randomisation time point, to ensure that they have had the chance to complete the intervention.

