#### Progression to full trial

Key indicators of study success and progression will be: (a) ability to recruit and (b) retain participants in the study (primary feasibility outcome). Progression from feasibility to a future definitive RCT would be warranted based on the criteria detailed below:Go: recruitment as planned (total trial *N* = 116, i.e. 58 participants per arm) and < 40% attrition (attrition = no follow-up assessment).Stop: recruitment below 70% of planned and/or attrition > 50%.

If recruitment and retention are between stop-and-go criteria (i.e. recruitment between 70 and 100% of planned and attrition between 40 and 50%): solid remedial action would need to be taken for the study to progress to a full RCT. This could include additional sites/recruitment methods or alterations to the intervention, based on qualitative feedback.

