### Assessment procedures

Online screening, consent and baseline assessment will be carried out before randomisation. Following the baseline assessment (week 0), eligible participants will be randomly allocated to either the FREED-M intervention or the control group. Participants in both groups will then complete three brief assessments (weeks 1–3), a post-intervention assessment (4 weeks post-randomisation) and a follow-up assessment (12 weeks post-randomisation); all of these will be completed online.

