### Outcome measures

#### Feasibility outcomes

Primary feasibility outcome: attrition rates at follow-up (the proportion of randomised participants who did not complete the follow-up assessment)Other feasibility outcomes: participant recruitment (proportions of randomised participants recruited from different sources; number of participants recruited per month); completion rates (proportion of randomised participants who completed all assessments); intervention uptake (proportion of randomised participants who accessed at least a part of the first intervention module); intervention completion rates (proportion of randomised participants who accessed each intervention module); intervention acceptability (proportion of participants in the intervention group with a rating of ≥ 4 on each feedback question, scored on a five-point Likert scale from 1 = did not like it at all/ not at all useful to 5 = best thing ever/extremely useful).

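### Interview approaches, confined to the FREED-M arm, are timed at week 12, when the attrition outcome is still being determined; they should wait until each participant's follow-up status is fixed

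*Protocol article*

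**What the plan says.** Under Interviews, the article plans qualitative interviews with "An estimated sample of around 20 participants, depending on inductive thematic saturation". On who is eligible it says: "Participants will be recruited purposively from the intervention group". Gender, age and baseline symptoms are given as examples of the sampling factors. On timing it says: "Participants will be approached for these interviews at the 12-week post-randomisation time point". The reason given is "to ensure that they have had the chance to complete the intervention".

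Assessment procedures places the last assessment at the same point: "a follow-up assessment (12 weeks post-randomisation); all of these will be completed online". Feasibility outcomes defines the primary feasibility outcome as "the proportion of randomised participants who did not complete the follow-up assessment". Progression to full trial makes the same quantity part of the Go rule, which needs full recruitment of 116 and "< 40% attrition (attrition = no follow-up assessment". Attrition between 40% and 50% is an intermediate zone that calls for remedial action, and attrition above 50% is Stop. The rule has no arm-specific component.

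Randomisation and blinding states that the research team is not blinded to allocation.

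**The concern.** The primary outcome is whether a participant completes an online questionnaire at week 12. An invitation to be interviewed, arriving while that questionnaire is outstanding, could act as a reminder. Only FREED-M participants can receive it. If it brings back some who would otherwise be lost, it lowers pooled attrition, the figure the Go rule uses, and it also alters the difference in attrition between the arms. Unlike sampling error, such an effect would be expected to push in one direction only.

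The decision is sensitive to small numbers because the Go threshold equals the planning assumption of 40% attrition under Sample size. If that assumption is right, the trial sits on the boundary and one or two participants can decide the classification.

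The stated reason for the timing does not need the overlap. The programme releases one of four animations per week and the post-intervention assessment is at week 4. Participants approached after their week-12 status is settled have had at least as much chance to finish.

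**Working it through.** **Inputs from the article.** N = 116, 58 per arm; assumed attrition 0.40; stated precision ±9% (all Sample size). Go needs attrition below 40% and Stop is above 50% (Progression to full trial). About 20 interviews, FREED-M arm only (Interviews).

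**Inputs assumed, not in the article.** m, the number approached before they have submitted the week-12 assessment: 10 to 25. c, the share of would-be losses among them that contact recovers: 10% to 50%. The article gives neither, nor the order of approach and submission. If no one is approached before submission, m = 0 and there is no effect.

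**Step 1: the plan's own figures.** 35/(1 − 0.4) = 58.3 per group, or 116.7 in total; the article uses 58 and 116. The half-width is 1.96 × √(0.4 × 0.6/116) = 0.089, which agrees with ±9%. The sample-size figures are not in question.

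**Step 2: the threshold in participants.** 46/116 = 39.7% meets the attrition criterion and 47/116 = 40.5% misses it. One participant is worth 1/116 = 0.86 points.

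**Step 3: no contact effect.** The chance of meeting the attrition criterion is P(X ≤ 46) with X ~ Bin(116, p). It is 51% at p = 0.40, 34% at p = 0.42 and 14% at p = 0.45.

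**Step 4: with contact.** Losses are the sum of Bin(116 − m, p) and Bin(m, p(1 − c)). The expected number recovered is m·p·c, so expected pooled attrition is p − m·p·c/116 and expected FREED-M attrition is p − m·p·c/58. At p = 0.40:

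| m | c | Expected recovered | Pooled attrition | FREED-M attrition | Chance of meeting criterion |
|---|---|---|---|---|---|
| 0 | any | 0 | 40.0% | 40.0% | 51% |
| 10 | 10% | 0.4 | 39.7% | 39.3% | 54% |
| 10 | 20% | 0.8 | 39.3% | 38.6% | 57% |
| 20 | 25% | 2.0 | 38.3% | 36.6% | 66% |
| 20 | 50% | 4.0 | 36.6% | 33.1% | 79% |
| 25 | 20% | 2.0 | 38.3% | 36.6% | 66% |
| 25 | 50% | 5.0 | 35.7% | 31.4% | 84% |

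The pooled shift therefore runs from 0.4/116 = 0.3 points to 5/116 = 4.3 points.

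**Step 5: away from the boundary.** With m = 25 and c = 20% to 50%, the chance at p = 0.42 rises from 34% to 49–72%. With m = 20 and c = 10% to 50%, the chance at p = 0.45 rises from 14% to 19–41%.

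**Step 6: which decision is at stake.** Stop on attrition needs at least 59 of 116 lost. Without any contact effect the probability of that is 1.2% at p = 0.40 and 3.4% at p = 0.42. Near the threshold the choice is between Go and the remedial zone, not between Go and Stop.

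**The case against.** The strongest objection is that the harm depends on a sequence the article does not state. It fixes a time point. It does not say that the approach precedes submission, that a researcher makes it in person, or how long the assessment stays open. A journal article commonly leaves such detail to the full protocol, and invitations may in practice follow submission, in which case nothing is lost. The sampling factors are also introduced as examples, so completion status may be among those used. Nothing in the Interviews section contradicts the outcome definition or the progression rule. The modelled shift is smaller than the ±9-point precision, and Go also requires full recruitment.

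Most of this stands, and it limits the point to a conditional one. A reader might infer that the plan biases its primary outcome or would turn a Stop into a Go. The documents support neither: the order is open, the effect may be zero, and attrition of 40% to 50% leads to remedial action. A reader might also infer that the interview colours the week-12 self-reports. Only the approach is timed at week 12, so that would need the interview itself to come before the questionnaire, which the article does not say. Nor does the article say whether a definitive trial would include such interviews.

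Two things remain. The timing is stated, not omitted: it coincides with the primary outcome and applies to one arm. And wide random error does not excuse an avoidable one-directional influence when the rule is stated as a fixed cut-off on pooled attrition.

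**Conclusion.** The point holds as a conditional risk that is cheap to remove. As written, the timing allows one-arm contact while the primary feasibility outcome is still being determined, for a reason that does not require it. The effect is zero if every approach follows submission. With 10 to 25 approached beforehand and 10% to 50% of would-be losses recovered, all assumed, expected pooled attrition at a true 40% falls by about 0.3 to 4.3 points and the chance of meeting the attrition criterion goes from 51% to 54–84%. It matters mainly close to the 40% threshold, which is where the plan expects to be, and mostly for Go versus remedial action. It is not a demonstrated bias, a contradiction or an error in the sample size.

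**What to change.** Amend the Interviews section so that no participant is approached for interview until their own week-12 assessment has been submitted or its completion window has closed. Non-completers stay eligible after that, so the interviews can still capture the views of people who dropped out. Report attrition by arm alongside the pooled figure.

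Trial progress states that recruitment began in November 2022. For anyone already approached, report whether the approach came before or after submission. Do not reclassify completed assessments as attrition: that would conflict with the outcome definition and bias the FREED-M arm in the opposite direction. If approaching after submission is already the practice, a sentence saying so is enough.

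The cost is one sentence of wording, slightly later interviews and slightly longer recall for interviewees.

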### Data analysis

#### Feasibility/clinical data

Outcomes, including feasibility outcomes, will be summarised as mean and standard deviation, median and interquartile range, frequency and proportion, or count and Poisson confidence interval, as appropriate. FREED-M intervention engagement metrics will be summarised for the intervention arm only. The potential outcomes for a future trial will be summarised appropriately overall and in each group. Completeness and variability of the outcome measures will be determined and used together as a guide to which might be best utilized as a primary outcome in a future definitive trial. As this is a feasibility trial, no formal statistical tests of differences between the groups will be conducted. Summary estimates will be used in calculating the sample size of the future large-scale RCT. All analyses will be conducted using STATA v14.

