### Study aims and progression to full trial

#### Our aims are twofold

Firstly, we aim to develop a smartphone-friendly multi-modal online decision-making tool (https://freedm.uk/) for young people with a first episode ED to increase motivation for treatment and change, help-seeking from primary care and attendance at specialist assessment/treatment and thus reduce DUED. Specifically, the intervention aims to increase motivation to change/seek treatment through psychoeducation and personalised feedback on symptoms and highlighting steps towards seeking and getting help.

Secondly, we aim to carry out a feasibility randomised controlled trial (RCT) comparing the intervention to a credible control intervention. The objectives of the proposed trial are to establish/estimate: (a) attrition rates at follow-up (primary feasibility outcome); (b) participant recruitment from different sources; (c) intervention uptake, completion rates and acceptability; (d) intervention effect sizes and standard deviations for outcomes to inform the sample size calculation for a large-scale RCT; (e) stakeholder views on the intervention, optimal delivery pathways and study procedures.

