### Randomisation and blinding

After the baseline assessment, participants will be randomly allocated to either the FREED-M intervention or signposted to the resources on the ED charity website (control group). A random allocation list will be created and maintained by the King’s Clinical Trials Unit using an online system to ensure allocation concealment. Minimisation will be used to balance groups for prognostic factors (anorexia nervosa vs other ED type; specialist referral in progress [yes/no]). Due to the nature of the study, neither participants nor the research team will be blinded to participant condition assignment. However, care will be taken to present interventions in both trial arms as equivalent to reduce participant expectancy biases.

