#### Clinical outcomes

ED-related outcomes: at baseline only, participants will complete a questionnaire on ED symptom onset abbreviated from a comprehensive onset interview from our early intervention studies [30–32] and report their height. At all assessment points (baseline, weeks 4 and 12) they will complete the Eating Disorder Diagnostic Scale (EDDS) [78], self-reported weight, questions on motivation and readiness to change [79] and questions on ED help-seeking. A short version of the EDDS and the questions on motivation and readiness to change will additionally be completed in weeks 1–3.Other clinical outcomes: questionnaires assessing depression and anxiety (PHQ-4) [80, 81], Disclosure Expectations Scale (DES) [82], social media beliefs and motivation for use (Social Media Use [83], Motivations for Social Media Use Scale [84]) and social impairment and functioning (WSAS-Y) [85] will be completed at baseline, weeks 4 and 12.

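### Planning estimates for the definitive RCT rest on raw group summaries, so for continuous scales they are less precise than the collected baseline data allow

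*Protocol article*

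**What the plan says.** Among the aims (Protocol article, Our aims are twofold), objective (d) is to estimate "intervention effect sizes and standard deviations for outcomes to inform the sample size calculation for a large-scale RCT".

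The Data analysis section (Feasibility/clinical data) gives the method: "Outcomes, including feasibility outcomes, will be summarised as mean and standard deviation, median and interquartile range, frequency and proportion", or as a count with a Poisson interval. On the candidate outcomes it says: "The potential outcomes for a future trial will be summarised appropriately overall and in each group". It then states the use: "Summary estimates will be used in calculating the sample size of the future large-scale RCT". The same paragraph rules out testing ("As this is a feasibility trial, no formal statistical tests of differences between the groups will be conducted") and leaves the future primary outcome open, to be guided by completeness and variability. It names no between-group difference with an interval, no residual SD and no baseline-to-follow-up correlation.

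Two other sections bear on this:
- Clinical outcomes: "At all assessment points (baseline, weeks 4 and 12) they will complete the Eating Disorder Diagnostic Scale (EDDS". The motivation and readiness questions, PHQ-4, DES and WSAS-Y follow the same schedule.
- Randomisation and blinding: "Minimisation will be used to balance groups for prognostic factors (anorexia nervosa vs other ED type; specialist referral in progress [yes/no".

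**The concern.** The section states both the summaries to be produced and the decision they will serve. An effect size built from raw group means ignores each participant's baseline score and the two factors that the protocol itself treats as prognostic. Where baseline and follow-up scores are correlated, that estimate has a wider interval than the same data could give.

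There is a second consequence for the later trial. If the definitive RCT is analysed with baseline adjustment, its size depends on the residual SD, or equivalently on the raw SD together with the correlation. The listed summaries supply the first ingredient and not the second.

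At stake is how well objective (d) is delivered. Progression does not depend on it, since the go and stop criteria use only recruitment and attrition.

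**Working it through.** **The plan's own figures.** The Sample size section takes 35 per arm and attrition of 0.4. 35/(1 - 0.4) = 58.3 per arm and 70/0.6 = 116.7 in total, against the stated 58 and 116. The precision for 40% attrition is 1.96 x sqrt(0.4 x 0.6/116) = 0.089, against the stated 9%. Both reproduce, and nothing below disputes them.

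**Inputs.** From the protocol: 35 completers per arm at follow-up. Assumed, because the protocol gives no value: a baseline-to-follow-up correlation rho of 0.3, 0.5 or 0.7. Assumed for illustration only: a target difference of 0.4 SD, 90% power and a two-sided 5% level for the future RCT.

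**Precision of the standardised difference.** The unadjusted SE is sqrt(2/35) = 0.239, so the 95% half-width is 1.96 x 0.239 = 0.469 SD. Adjusting for the baseline value multiplies the variance by (1 - rho^2), so the half-width becomes 0.469 x sqrt(1 - rho^2).

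**Size of the future RCT.** Per arm, n = 2 x (1.96 + 1.2816)^2 x (1 - rho^2)/0.4^2. Sizing on the raw SD when the analysis is baseline-adjusted inflates n by 1/(1 - rho^2).

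| rho | 95% half-width, 35 per arm (SD units) | Inflation if sized on raw SD alone | Illustrative n per arm |
|---|---|---|---|
| 0 (unadjusted) | 0.469 | 1.00 | 132 |
| 0.3 | 0.447 | 1.10 | 120 |
| 0.5 | 0.406 | 1.33 | 99 |
| 0.7 | 0.335 | 1.96 | 67 |

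**How far rho can be trusted.** If 0.5 were observed in 70 responders, the Fisher-z interval is tanh(0.549 ± 1.96/sqrt(67)), which is 0.30 to 0.66. A cautious planner using the lower limit would go from 132 to 120 per arm, a saving of 9%. The point estimate would give 99, a saving of 25%.

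**Limits.** These are large-sample formulae for the baseline value only. They claim no gain from the minimisation factors and ignore the small cost of the covariate degrees of freedom. They apply to continuous scales. The 35 per arm refers to the 12-week follow-up; the protocol gives no separate figure for week 4.

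**The case against.** The text never says that estimates will be unadjusted. It says that outcomes will be summarised as appropriate, and covariate adjustment is a detail that an article may leave to an analysis plan. The raw SD is what objective (d) asks for. The correlation can still be computed later, because the paired data will exist. Adjustment changes no decision in this trial, and an interval of 0.406 SD either side is still too wide to settle a target effect.

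Most of this stands, and it limits the point. What remains is that every summary the section lists is a raw one, and the section ties those summaries to the future sample size. Naming the missing quantities is therefore a concrete improvement to a stated method. The exclusion of formal tests is no obstacle, since an adjusted difference with an interval and no p-value respects it.

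Two stronger readings are tempting, and the documents do not support them:
- **A reader might infer that the raw SD is the wrong variance.** It is a correct quantity. It oversizes the RCT only if that trial uses baseline adjustment (ANCOVA) and no (1 - rho^2) factor is applied, and the protocol fixes neither. The result would be excess sample size, not an underpowered trial.
- **A reader might infer that chance baseline imbalance biases the raw comparison.** Under randomisation it averages zero and is already contained in the unadjusted SE of 0.239. Imbalance among the roughly 60% who respond is a separate matter. Adjustment reduces it only as far as the baseline value and the two factors explain it.

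**Conclusion.** The point holds as a modest gain in efficiency and does not show an error in any stated figure. For continuous candidate scales, the planned summaries give effect estimates with a 95% half-width of 0.469 SD, where 0.447, 0.406 or 0.335 SD is attainable at assumed rho 0.3, 0.5 or 0.7. A definitive RCT analysed with baseline adjustment but sized on the raw SD alone would be larger than needed by a factor of 1.10, 1.33 or 1.96. With a cautious value of rho, the practical saving may be nearer 9% than 25%.

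The conclusion rests on assumed correlations, on outcomes scored as continuous, and on 35 completers per arm. It does not carry over to binary or time-based endpoints such as attendance at specialist assessment or DUED, either of which could become the future primary outcome. Nor does adjustment make 35 per arm a reliable sole source for the target effect.

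**What to change.** In Feasibility/clinical data, keep the raw summaries overall and by arm. For continuous candidate outcomes measured at baseline, add:

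1. The between-group difference at weeks 4 and 12 (where measured) from a linear model with arm, the baseline value of that outcome and the two minimisation factors, with a 95% CI and no p-value.
2. The residual SD from that model.
3. The baseline-to-follow-up correlation with its 95% CI.

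Then state that, if the definitive RCT is to be analysed with baseline adjustment, its size will be based on the raw SD with a (1 - rho^2) factor, taking a conservative lower value of rho.

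The cost is a few sentences and some extra model fits, with no more participants or assessments. There are two small downsides. Three covariate degrees of freedom are spent with about 70 responders, and rho is imprecisely estimated, which the conservative value is there to handle.

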**Methods:**

We will carry out a randomised controlled feasibility trial comparing the FREED-M tool with a control intervention where individuals are sign-posted to an ED charity website. The objectives of the proposed trial are to establish/estimate: (a) attrition rates at follow-up (primary feasibility outcome); (b) participant recruitment; (c) intervention uptake, completion rates and acceptability; (d) intervention effect sizes and standard deviations for outcomes to inform the sample size calculation for a large-scale randomised controlled trial (RCT); (e) stakeholder views on the intervention.

We aim to recruit 116 participants (young people, aged 16–25, with first episode ED) from primary care, schools and universities, ED services and social media. Online assessments will be carried out at baseline, end of intervention and follow-up (weeks 0, 4 and 12 post-randomisation, respectively). Outcomes will include motivation and readiness to change, attitudes and intentions towards help-seeking, ED symptoms, mood and social functioning, and health-related quality of life. Additionally, we will carry out a qualitative evaluation of participants’ views of the intervention and study design.

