### Sample size

We have chosen a sample size of *n* = 35 per group, which is at the upper end recommended for feasibility trials [76]. We assume an attrition to follow-up rate (a) of 0.4. This is based on data from our ongoing European Union-consortium of internet-based prevention and treatment of common mental disorders, including EDs. Applying an attrition correction factor of 1/(1-a), we will need a sample size of *n* = 116, i.e. 58 participants/group. Assuming 116 eligible participants enrol, we will be able to estimate a 40% attrition rate within a 95% confidence interval of ± 9%.

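### Objective (d) offers the observed effect size as an input to the definitive RCT's sample size, without restriction, although about 35 completers per arm estimate it only to within ±0.47 SD

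*Protocol article*

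**What the plan says.** Objective (d), under the heading on the study's two aims, is to establish or estimate "intervention effect sizes and standard deviations for outcomes to inform the sample size calculation for a large-scale RCT". The Methods part of the abstract gives the same objective. The section on feasibility and clinical data says that "Summary estimates will be used in calculating the sample size of the future large-scale RCT" and that "no formal statistical tests of differences between the groups will be conducted".

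The Sample size section chooses "35 per group, which is at the upper end recommended for feasibility trials". It continues with "We assume an attrition to follow-up rate (a) of 0.4" and inflates to 58 per group, 116 in all. The only precision it states is for attrition: 40% with a 95% interval of ±9%. It gives no precision for an effect size. The article names no smallest worthwhile difference for the RCT and no external source for its target effect, and it does not say that the observed effect will be kept out of the calculation.

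**The concern.** A trial of this size can give usable values for nuisance parameters such as SDs, control-arm rates, baseline-to-follow-up correlation and attrition. It cannot estimate the treatment effect precisely enough to power another trial. The required sample size varies with the inverse square of the target difference, so sampling error in the effect is magnified in the sample size. A chance-high estimate leads to an underpowered RCT. A chance-low one leads to an RCT far larger than needed, and a zero or negative one gives no sample size at all. Objective (d) puts effect sizes and SDs on the same footing as inputs, so a reader following the plan could use the observed effect as the target difference.

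**Working it through.** **The plan's own figures.** 35/(1 − 0.4) = 58.3 per group and 70/(1 − 0.4) = 116.7 in total, which agrees with 58 and 116. The half-width for 40% attrition is 1.96 × √(0.4 × 0.6/116) = 0.089, that is ±9%. Both reproduce and are not in question.

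**Inputs.** From the Sample size section: 35 completers per arm expected, 58 per arm randomised. Assumed, because the article gives none of them: a continuous primary outcome, two-sided 5%, 90% power, and a true standardised effect d between 0.2 and 0.5.

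**Precision of the effect.** SE(d) ≈ √(2/n).
- n = 35 per arm: √(2/35) = 0.239; 1.96 × 0.239 = 0.47.
- n = 58 per arm: √(2/58) = 0.186; 1.96 × 0.186 = 0.36.

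With 35 per arm, an observed d of 0.3 has a 95% interval of about −0.17 to 0.77. An observed 0.5 has about 0.03 to 0.97.

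**Precision of the SD, for contrast.** With 2 × 35 − 2 = 68 degrees of freedom, the 95% interval for a pooled SD runs from about 14% below to 20% above the estimate. The one-sided 80% upper limit is 1.082 times the estimate.

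**Consequence if the point estimate is the target difference.** The RCT needs n per arm = 2 × (1.96 + 1.282)²/d² = 21.0/d², which is 526, 234, 132 and 85 at d = 0.2, 0.3, 0.4 and 0.5. Because n varies as 1/d², the computed n is under half of what is needed when the observed effect exceeds √2 × d. It is over double, or not finite, when the observed effect is below d/√2. Treating the observed effect as normal with mean d and SE 0.239:

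| True d | n under half: P(Z > 0.414d/0.239) | n over double or none: P(Z < −0.293d/0.239) | Total | Of which observed effect ≤ 0 |
|---|---|---|---|---|
| 0.2 | 36% | 40% | 77% | 20% |
| 0.3 | 30% | 36% | 66% | 10% |
| 0.4 | 24% | 31% | 56% | 5% |
| 0.5 | 19% | 27% | 46% | 2% |

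The totals are taken before rounding. The power level cancels out of these probabilities, so they are the same at 80%. A simulation that also lets the SD be estimated agrees to within about one percentage point in the totals (47% at d = 0.5). With all 58 per arm retained, the same formula gives 70%, 57%, 45% and 35%.

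At true d = 0.3, among feasibility trials with a positive observed effect, 47% lead to an RCT with true power below 80%, and 23% to one below 50%, when 90% was intended.

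**The case against.** The strongest reply is that the text says less than one might read into it. A reader might infer that the RCT will be sized on the observed effect. Objective (d) says only that the estimates are to inform the calculation, and the analysis section speaks of summary estimates without naming which. Taken alone, that sentence could mean SDs, rates and attrition, and using those would be sound. This stands, and it is why the probabilities above are conditional on the point estimate being the sole target difference, a rule the article does not state. It does not remove the point: objective (d) names effect sizes as an input, the analysis section says the estimates will be used in the calculation, and no other basis for the target difference appears.

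A reader might also infer that the trial fails its purpose, or that a chance-negative effect would end the programme. The article does not support that. The primary feasibility outcome is attrition, the sample size is justified by its precision, and the progression criteria use recruitment and attrition only. Recruitment, uptake, acceptability, SDs, completeness and stakeholder views would still inform the RCT.

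Finally, a reader might fault the absence of formal between-group tests or of adjusted between-arm models. Omitting tests is sound in a feasibility trial, and modelling detail is something an article may leave to the full protocol or SAP. Neither is a defect here.

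The size of the problem also depends on the true effect. At d = 0.5 the observed effect is zero or negative only 2% of the time, though the RCT's size would still be off by a factor of 2 or more in nearly half of cases.

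**Conclusion.** The point holds in a limited form. The article offers the observed effect size as a sample-size input, does not restrict that use, and gives no alternative basis for the target difference. The expected 35 completers per arm estimate a standardised effect only to ±0.47, and full retention improves this only to ±0.36. If the point estimate became the target difference, a mis-sizing by a factor of 2 or more, or no finite size, would occur in roughly 46% to 77% of cases for true effects of 0.5 down to 0.2. This rests on an assumed continuous outcome, two-sided testing at 5% and the assumed range of d; the primary outcome of the RCT is still to be chosen.

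Nothing in the conduct, primary outcome or progression decision of this trial changes, and the RCT's own protocol could still set its target difference properly. It should be fixed, but the trial does not depend on it.

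**What to change.** Reword objective (d), in the abstract and the main text, and the sentence in the feasibility and clinical data section, to say three things.

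1. This trial supplies only nuisance parameters for the RCT's sample size: the SD (preferably with an upper confidence limit, for example the one-sided 80% limit, about 8% above the estimate at 68 degrees of freedom), control-arm rates, baseline-to-follow-up correlation, attrition and outcome completeness.
2. The RCT's target difference will be a smallest worthwhile difference, or come from external evidence, set independently of the effect observed here.
3. Any between-arm effect size will be reported with its 95% confidence interval as descriptive and not for powering.

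The cost is a few sentences and an interval beside each reported effect size. It needs no further participants and no further data. The change should be made before the RCT is sized; since recruitment has already begun, it can be recorded as an amendment or stated in the SAP.
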